## Abstract

**Background:**

Promotion of healthy lifestyles in children focuses predominantly on proper nutrition and physical activity, elements now widely recognised as essential for a healthy life. Systematic reviews have shown that nature-related activities also enhance general well-being as reflected in increased physical activity, a healthier diet, reduced stress and better sleep. Recent research suggests that many young children in Hong Kong between the ages of two and four in Hong Kong are more sedentary than recommended and seldom participate in active play, placing them at risk of becoming overweight or obese. The proposed project aims to investigate whether connecting families to nature positively influences physical activity (i.e., active playtime) and healthy eating routines in children aged 2 to 4.

**Methods:**

We recently conducted a pilot study in Hong Kong to develop a programme, Play & Grow, based on the most successful evidence-based international preschool interventions. In addition to adopting the healthy eating and physical activity elements of these interventions, this project will additionally include a third novel element of Connectedness to nature: discovering nature through games and awareness of sounds, touch, smells, and temperature. To test the effectiveness of this modified intervention, a randomised controlled trial (RCT) involving 240 families with children aged 2 to 4 will be conducted. Families and children will take part in weekly one-hour activity sessions for 10-weeks. Lifestyle-related habits will be assessed before and immediately after the 10-week intervention, with follow up testing at 6 and 12 months’ post intervention.

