#### Hypotheses

After completing the Play & Grow program (10-week, 6 and 12 months), *children* in the IG, when compared with the WLCG, will: (1) eat healthier, have a higher responsiveness to satiety, be less fussy with food, have less food neophobia; eat more fruit, vegetables and less obesogenic foods; (2) be more active, less sedentary and (3) have a higher Connectedness to nature, reflected in increased time spent outdoors. The *parents* in the IG will: (1) know more about healthy eating, active play and Connectedness to nature; and 2) gain *general* and *specific* parenting practices, including role-modelling for healthy habits.

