#### Intervention

Each session will present, discuss and enact a certain parenting practice (Table 1). The Play & Grow will have educational strategies including instructions, parental peer support and group discussions, and homework tasks, in accordance with the elements developed in our Play & Grow pilot study. Each session will comprise: (i) 15 min of guided active play involving both children and parents; (ii) 15 min of interactive education and skill development for parents; simultaneous supervised active play with foods for children, to promote acceptance of vegetables, and (iii) 15 min of guided active nature games outdoors, involving both children and parents. The sessions will incorporate a lifestyle component, for example: eating, active play and connectedness to nature). These will target the parents’ knowledge and skills on how to introduce and maintain their child’s correct lifestyle routines. A group leader and co-leader with healthcare backgrounds (and trained by the PI during the Play & Grow pilot study) will facilitate the sessions involving 4 to 5 parent-child dyads.

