#### The novel Connectedness to nature element

The most appropriate way of instilling habits related to nature is to stimulate children's natural curiosity as early in life as possible. This could be done by involving caregivers and educating them about nature-related activities [30, 38–41]. In adults, research demonstrates a correlation between learning about the nature and the length of time spent in nature [42]. Connectedness to nature is described as including basic environmental knowledge, environmental sensitivity and awareness, as well as a commitment to protect nature [28]. In the proposed intervention, we will employ environmental education and nature-related activities to help participating families develop skills conducive to improving playtime and eating habits in children. Examples of the additional elements that make up an 1/3 of the programme are: i) inclusion of active nature games outdoors that involve both children and parents focusing on motor skills, discovering nature, practicing awareness to sounds, touch, smells, temperature, ii) group activities with other families and members, practicing nature related activities, iii) nature homework with follow-ups (collect objects found in nature and make art or grow their own plants), iv) environmental care training (paper waste, water saving, recycling), and v) studying new vegetables and cooking together with them (avocado, using the avocado to make a boat, turning the avocado into guacamole, etc.).

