### Primary outcomes and their assessments

Measurements will be conducted prior to and after the 10-week intervention, with further follow up assessments at 6 and 12 months in order to observe both the short and long term outcomes (Table 2). Although many variables will be measured in both children and participating parents, we carefully chose a few questionnaires, which covered multiple variables.

**Table 2 Tab2:** Intervention outcome instruments

Intervention Outcomes	Source	Baseline	End-of-intervention	6-month Follow-up	12-month Follow-up
Parent					
General Parenting Practices					
Knowledge of children’s:					
Feeding	PCFQ	✕	✕		
Nutrition	NKQ	✕	✕		
Active play	Pre-PAQ	✕	✕		
Connectedness to nature	NRS (self-developed)	✕	✕		
Correct practices:					
Feeding	CFPQ	✕	✕	✕	✕
Nutrition	NKQ	✕	✕	✕	✕
Active play	Pre-PAQ				
Connectedness to nature	NRS (self-developed)	✕	✕	✕	✕
Parental self-efficacy for correct practices	INFANT scale	✕	✕	✕	✕
Parental modelling of healthy habits, diet, active play, connectedness to nature	INFANT scale	✕	✕	✕	✕
Limit setting	Self-developed scale	✕	✕	✕	✕
Specific Parenting Practices					
Diet	CEBQ	✕	✕	✕	✕
Active Play	IPAQ, Pre-PAQ	✕	✕	✕	✕
Sedentary time	Pre-PAQ	✕	✕	✕	✕
Connectedness to nature	NRS (self-developed)	✕	✕	✕	✕
Child					
Eating Habits	EPAQ	✕	✕	✕	✕
Physical Activity	Pre-PAQ	✕	✕	✕	✕
Sedentary Behaviour	Pre-PAQ	✕	✕	✕	✕
Food Neophobia	PCNS	✕	✕	✕	✕
Connectedness to nature	NRS (self-developed)	✕	✕	✕	✕

Please see detailed references in proposal’s text

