#### Nature relatedness

Connectedness to nature in children will be measured using a short, age-adjusted NRS scale that will be validated in Stage 1. The scale uses a number of specific questions about environmental sensitivity, distance from home to natural areas, how often and how long the family spends in nature and what nature-related activities are done, including questions on recycling, garbage sorting and saving water.

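### At the 10-week visit, time spent in Play & Grow sessions can be reported as active play and time in nature, in the intervention arm only

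*Protocol article*

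**What the plan says.** On timing, the abstract has "Lifestyle-related habits will be assessed before and immediately after the 10-week intervention". The section on primary outcomes and their assessments agrees: "Measurements will be conducted prior to and after the 10-week intervention, with further follow up assessments at 6 and 12 months".

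On session content, the abstract describes "weekly one-hour activity sessions for 10-weeks". The Intervention section lists three parts per session. The first is "15 min of guided active play involving both children and parents" and the last is "15 min of guided active nature games outdoors, involving both children and parents". The middle 15 minutes are education for the parents, during which the children have supervised play with foods that the article also calls active. The section on the nature element adds "nature homework with follow-ups (collect objects found in nature and make art or grow their own plants".

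On outcomes, the Hypotheses section expects intervention children to be more active and to "have a higher Connectedness to nature, reflected in increased time spent outdoors", at 10 weeks as well as at 6 and 12 months. Activity is measured by the Pre-PAQ. Under Nature relatedness, the NRS is said to ask "how often and how long the family spends in nature and what nature-related activities are done". The Participants section wants the same caregiver to complete the questionnaires, and offers the programme to the waiting-list arm only once the study is complete.

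**The concern.** The hypotheses are about habits: what the child and family do in ordinary life. The first post-baseline questionnaire follows directly on weekly sessions that consist largely of the behaviours being asked about. If the recall period reaches back over a programme week, a caregiver who answers truthfully may include the session, and only intervention caregivers can do so. A family that attended but changed nothing at home could then score higher on active play and on time in nature.

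The hypotheses name 10 weeks beside 6 and 12 months without singling out one visit, so a 10-week difference may be read as evidence that habits changed. The article also plans a later mediator study of which components worked. If 10-week time in nature were used as a mediator, part of it could simply restate exposure to the sessions. Once session and home time have been reported as one figure, no analysis can separate them. The rule has to be set when the data are collected.

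**Working it through.** **The plan's own figure.** The article gives 100 families per group for power 0.8 at α = 0.05, with no mean or SD, so the number cannot be rebuilt from its inputs. It can be turned into a detectable difference (two-sided test assumed): (1.960 + 0.842) × √(2/100) = 0.396 SD. This serves only as a yardstick here; the sample size is not in dispute.

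**Inputs from the Intervention section**
- Outdoor time: 15 min per weekly session.
- Active play: 15 + 15 = 30 min (guided play plus nature games), or 45 min if the children's play with foods is also counted.
- The listed parts add to 45 min, while the abstract says one hour. Only the listed parts are used.
- Homework has no stated duration and is left out.

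**Assumptions, not in the article**
- SD of daily minutes between 30 and 90.
- Full attendance, every session minute counted, and none of it replacing time the family would have spent outdoors anyway.

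**Case A: past-week recall that includes a session**
- Outdoors: 15/7 = 2.1 min/day.
- Active play: 30/7 = 4.3 to 45/7 = 6.4 min/day.
- If 80% of sessions are attended, multiply by 0.8: 1.7 and 3.4 to 5.1 min/day.

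**Case B: recall of two weekend days, one with a session.** This is illustrative. Weekend scheduling is reported for the pilot; the trial's session day is not stated.
- Outdoors: 15/2 = 7.5 min/day.
- Active play: 30/2 = 15 to 45/2 = 22.5 min/day.

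**Case C: window wholly after the last session.** Sessions contribute 0.

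Dividing by the assumed SD gives d. The chance that session time alone produces a significant result in the programme's favour is Φ(d × √50 − 1.96), against 2.5% with no difference at all.

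| Case | Outcome | d (SD 90 to 30) | Share of 0.396 SD | Chance of significance |
|---|---|---|---|---|
| A | Outdoors | 0.02–0.07 | 6–18% | 4–7% |
| A | Active play | 0.05–0.21 | 12–54% | 5–33% |
| B | Outdoors | 0.08–0.25 | 21–63% | 9–42% |
| B | Active play | 0.17–0.75 | 42–189% | 22% to nearly 100% |
| C | Both | 0 | 0 | 2.5% |

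**Frequency item.** Minutes may understate the effect on an item that asks how often. A session counted as an outing adds one per week. With an assumed usual 1 to 3 outings per week, that is 1/1 = 100% down to 1/3 = 33%.

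**The case against.** The strongest reply is that everything turns on the recall window and the completion instructions. These normally sit in the questionnaires or the full protocol, which an article condenses. If the window starts after the last session, or the instructions already exclude programme time, nothing is left of the point. That stands, and it is why the point is conditional. It does not remove the point: the timing, the session content and the NRS content are stated choices that overlap, and the NRS is self-developed and still to be finalised in Stage 1.

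Size is the second reply. On a weekly average the outdoor contribution is about 2 min/day, which is small on any of the assumed SDs. The large values need short recall that happens to cover a session day, which the article does not describe. Session time may also replace outdoor time the family would have had anyway. All of this stands.

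Third, homework done at home is arguably the routine the programme hopes to create, so excluding it could remove real change. This stands too, and the fix leaves homework in.

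Fourth, the design already separates immediate from long-term effects and includes 6- and 12-month visits. That is correct, and those visits are the natural place for the claim about habits.

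**Conclusion.** The point holds in conditional form. At 10 weeks, the Pre-PAQ activity items and the NRS time and frequency items can include session time in one arm only, and any such inclusion favours the intervention. The contribution is 0 if recall starts after the last session. It is about 2 min/day outdoors and 4 to 6 min/day of active play under weekly recall, or 0.02 to 0.21 SD on the assumed SDs. It is more if a short recall covers a session day.

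A reader might infer four stronger things that the article does not support:
- That the 10-week effect does measure attendance rather than habit. Without the recall window, one can say only that it may do so in part.
- That the session contribution matches the 25% change used in the sample size section. That figure concerns vegetable consumption and is no benchmark for time in nature.
- That the eating outcomes are inflated in the same way. Counting session minutes gives no mechanism for that.
- That a fall from 10 weeks to 6 or 12 months would show a habit that never formed. The later visits lie outside the programme and are free of this problem, but the article gives no ground for predicting such a pattern.

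**What to change.** At the 10-week visit, in both arms, do one of two things:
- start the recall window after the last session, which means completing the questionnaires at least one window length later; or
- add one instruction to the NRS time and frequency items and to the Pre-PAQ activity items not to count time in Play & Grow sessions.

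Activity at home, including homework, may still be counted. In the analysis and report, rest the claim of changed activity and outdoor habits on the 6- and 12-month visits, and read the 10-week value as an immediate response.

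The second option costs one line of instruction and both need one sentence on interpretation; the sample and the choice of instruments stay as they are. There are drawbacks: the 10-week effect may look slightly smaller, caregivers must separate session time from home time, and the instruction adds a line to a validated questionnaire (the Pre-PAQ). For the NRS, the line can be built in while the scale is finalised in Stage 1.

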**Discussion:**

A novel measuring tool created specifically for assessing Connectedness to nature, Nature Relatedness Scale (NRS), will be validated and tested for reliability prior to the RCT. The results of the RCT are intended to be used to understand which components of the intervention are most effective. The objectives of this project will be achieved over a 30-month period and will contribute to the research that examines key components of successful healthy lifestyle promotion programmes during early childhood. We predict that the inclusion of Connectedness to nature will significantly improve recognised preschool interventions. Finally, the aim of targeting family involvement will hopefully increase the sustainability of longer-term lifestyle modifications in children.

**Trial registration:**

ClinicalTrials.gov, NCT02715544. Registered 22 March 2016

## Background

Proper nutrition and physical activity are essential for a healthy life [1]. Modern-day children practice unhealthy habits and routines; they play indoors, engage in sedentary activities, eat poorly and get insufficient sleep. Lifestyles are generally becoming unhealthier worldwide, and Hong Kong is no exception [2, 3]. The urban environment is criticised for being ‘toxic’, promoting the ‘nature-deficit’ phenomenon, and for stimulating less physical activity in young children [4, 5]. In Hong Kong, the majority of people live in densely populated areas, moving within a concrete labyrinth with little exposure to nature. The prevalence of overweight and obesity amongst Hong Kong children has become an increasingly prominent public health concern. A recent study of the Hong Kong population, conducted in 2013, reported that children as young as 6 months were overweight/obese and by the age of 2 years of age almost 5 % of the territory’s children were overweight/obese [2, 3, 6]. Any routines, healthy and unhealthy that get introduced in early childhood may stay for life, strongly suggesting that interventions promoting healthy living should start as early as possible [7]. For these reasons, we have chosen to target families with children aged 2 to 4 in our proposed research. It is widely accepted amongst the caregivers that preschool children are sufficiently active and as a result of this belief is that preschool children are often overlooked in physical activity research [7]. This belief, however, does not always reflect the real situation. The family setting provides the most powerful influence on preschool children; consequently, many of the risk factors for obesity in the preschool years are rooted in the family context [8]. Parents have the capacity to impact their children’s emerging food choices with their knowledge of nutrition, and their parenting style and modelling [9]. The strongest predictor of vegetable consumption in 2–6 year old children is parental consumption, and when it comes to negative eating behaviour in this age group, this can be modified if handled properly [10]. Furthermore, children with active parents also tend to be more active [11]. In Hong Kong, parents often adopt inappropriate strategies in managing the physical activities and dietary habits of their children, such as encouraging overeating i.e. "force feeding", and allowing children to watch TV while eating, etc. [2, 3, 6]. We therefore intend to conduct a family intervention, targeting children’s caregivers, as it is well-confirmed that they are responsible for introducing the lifestyle routines in young children and thus play one of the biggest roles in influencing their habits [12]. Although grandparents and domestic helpers and are also highly involved in taking care of the children of in Hong Kong, we targeted families with parents as the primary caregivers and not domestic helpers in order to test our hypothesis in a more controlled and homogenous group. The tools which are often utilised by parents to manage some problematic behaviour in children (e.g., food fussiness) [13] are documented to firstly improve *general* parenting and secondly, the parenting practices in *specific* situations [13]. A recent Cochrane review reported only a marginally significant improvement in body weight after some interventions and little to no effect on dietary or physical activity behaviours [14]. Hence, developing new lifestyle intervention programs for preschool children and testing these is highly relevant.

Time spent in nature has also proven to be beneficial for health and wellbeing. The systematic reviews conducted recently have pointed out that nature-related activities enhance general well-being and lead to increased physical activity, a healthier diet, improved sleep and reduced overall stress [15–18]. Worldwide, the most current programmes promoting a healthy lifestyle for children focus almost exclusively on diet and physical activity [19], but few take into consideration a family’s interactions with nature. We suggest that this emerging research area, known as Connectedness to nature or Nature Relatedness [20], is highly related to healthy lifestyle. Unhealthy lifestyle is often explained by environmental factors, while more time spent outdoors in a natural environment is reflected in healthy life patterns [15, 21].

We recently conducted a pilot study in Hong Kong, Play & Grow learning, which is based on the most successful preschool interventions from Sweden and Australia [22, 23]. The results of the pilot work helped formulate the basis of the present project by incorporating the healthy eating and physical activity elements of Play & Grow to which we also included a third novel element; Connectedness to nature. The proposed project will examine this modified Play & Grow intervention aimed at promoting healthy lifestyle in preschool children (aged 2 to 4) through the combined intervention of healthy eating, active play and connectedness to nature habits to children and their families.

The strategies outlined in this study are particularly appropriate to Hong Kong for several reasons. First, most Hong Kong children in primary schools fail to reach the physical activity levels recommended by the health authorities, and moreover, their increased sedentary habits lead to deterioration in health [2, 3, 24]. Second, Hong Kong children’s food habits fail to meet recommended nutritional standards: the major source of energy intake derives from calorie-dense foods, saturated fats and sugar [6], negatively influencing the territory’s obesity levels [6]. Third, this unhealthy lifestyle has negative consequences not only on general well-being but also academic performance; an issue of great concern to Hong Kong parents. It is therefore hoped that the proposed project will bring sustainable health benefits to Hong Kong’s population in a long run. These positive changes and benefits will hopefully in turn lead to reduced prevalence of obesity amongst children in Hong Kong, and a concomitant decrease in healthcare related costs.

In addition, this pioneering project will have scientific value in development of several important protocols and measurement instruments, including our Nature Relatedness Scale. Existing instruments for nature relatedness are applicable only to adults and have not yet been tested in Asia; thus, our new instrument will contribute to international research in this field, which has been relatively sparse to date.

### Conceptual influences

Children’s optimal development is promoted by active family involvement (Patterson’s Social Interaction Learning Theory) [25]. One of the most effective lifestyle parenting programmes is INFANT (Infant Feeding Activity and Nutrition Trial), which focuses on parenting skills to support the development of healthy lifestyle behaviours in infancy and employs an anticipatory guidance framework (AGF) [26]. This framework helps the parents manage certain behaviours in advance rather than managing the problems once they have materialised [26]. The modified Play & Grow intervention proposed here will use the same AGF in addressing the eating, sedentary habits of children aged 2 to 4. According to our conceptual model (Fig. 1), the AGF and parenting support theory ‘children’s psychological and behavioural goals, logical and natural consequences and encouragement’ [27], will aid parents in their *general parenting skills* and knowledge on better-practice eating, active play and Connectedness to nature behaviours in children. This will hopefully modify *specific parenting practices* (e.g., eating, active play and Connectedness to nature routines) that will consequently result in improved family lifestyle and child health.

